**Methods:**

A single-blinded, randomized, and parallel-group clinical trial will be conducted with dyads of parents or caregivers and children aged between 36 and 60 months, recruited from kindergartens and schools of Bauru, São Paulo. The determination of sample size resulted in a total of 104 dyads of parents and children, considering a power of 80%, a significance level of 5%, and an attrition of 30%. This sample will be randomly assigned to test and control groups, being divided in 52 dyads per group according to the health literacy levels of parents and the age, gender, and oral health status of children. Every 2 weeks, only participants in the test group will receive messages via WhatsApp containing preventive and education-related ECC information. The dyads will visit the dentist every 3 months during a year for the assessment of primary outcomes (sugar consumption and the International Caries Detection and Assessment System, visible plaque, and community periodontal indices) and to receive dental care measures. Secondary outcomes (electronic health literacy and general perceived self-efficacy) will be determined only at baseline and after 12-month follow-up. The quality of randomization will be evaluated throughout the study, comparing the test and control groups systematically by Student t tests for continuous variables and chi-square tests for categorical variables. Listwise deletion method will be applied in cases of dropouts, if the missing values satisfy the criteria of missing completely at random; otherwise, multiple imputation data strategy will be conducted. The Kolmogorov-Smirnov and Levene tests will be used to determine the normality and homogeneity of data, respectively, which will indicate further statistical analyses for elucidating significant differences between groups (P<.05). A Student t test or Mann-Whitney U test will be employed for parametric or nonparametric analyses, respectively.

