### Eligibility Criteria

Dyads of parents and children will be recruited during visits to kindergartens and schools located in Bauru, Brazil, if satisfying the following inclusion criteria: children aged between 36 and 60 months; children at high risk of dental caries, according to the criteria described in the Caries Risk Assessment Form for 0- to 5-Year Olds [18]; children with a score ≤3, according to the criteria of ICDAS [19]; parents or caregivers with a mobile phone with internet access; parents or caregivers who accept to participate in all stages of research by signing a written informed consent form; and parents or caregivers who already have WhatsApp Messenger app installed on their smartphones, or those who agree to install it for the participation in the study.

The risk of dental caries will be based on the information collected during the anamnesis and clinical examination, which will be performed by a trained and calibrated dentist. Children will be examined in a dental clinic, using compressed air and artificial lighting, following the ICDAS criteria [19], the visible plaque index (VPI) [20], and the community periodontal index of treatment needs (CPITN) [21].

The oral hygiene level of children will be determined by the observation of visible plaque on the buccal dental surfaces of 6 deciduous teeth (#55, #53, #51, #71, #73, and #75) [20]. The periodontal health status of children will be assessed considering 3 parameters of analysis: presence of bleeding, detection of dental calculus, and depth of gingival sulcus [21]. According to Almeida et al [22], this study will classify deciduous teeth with 1 of 3 different scores: healthy (0), gingival bleeding (1), and presence of dental calculus (2).

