### Study Outcome Measures

The primary outcomes will be related to the oral health status of children and the risk factors for ECC. For that, ICDAS, VPI, and CPITN indices will be determined for the recruitment of participants at baseline and 3-, 6-, 9-, and 12-month follow-ups.

The secondary outcomes will be related to the measurement of the influence of educative strategies on parents or caregivers, considering their patterns of sugar consumption, their level of eHealth literacy, and their individual perceptions about their own ability in executing specific activities. These data will be collected at baseline and after the 12-month follow-up using the questionnaire for sugar consumption [26], the instruments eHEALS [23], and General Perceived Self-Efficacy Scale (GSES) [27], respectively. In addition, the results of eHEALS will be applied for the recruitment of participants.

GSES measures the individual’s beliefs about their cognitive, motivational, behavioral, and affective skills needed to perform particular tasks. It comprises 10 questions with answers arranged in a 4-point Likert scale, with options ranging from *not at all true* through *exactly true*. The total score ranges between 10 and 40 points, with greater scores indicating higher overall perceived self-efficacy of individuals [27].

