### Data Analysis

Statistical analysis will be performed using SPSS Statistics software 21.0 (IBM SPSS Statistics). The data will be presented with descriptive statistics, being examined for lost values, outliers, normality, and homogeneity. To investigate the quality of randomization, potential differences between the characteristics of participants of the test and control groups will be determined systematically, applying Student *t* tests for continuous variables and chi-square test for categorical variables. Listwise deletion method will be adopted in cases of dropouts, if the lost values satisfy the criteria of the missing data completely at random; otherwise, multiple imputation data strategy will be used. The Kolmogorov-Smirnov and Levene tests will be used to analyze the normality and homogeneity of data, determining further statistical tests for detecting differences between groups (*P*<.05). A Student *t* test or Mann-Whitney *U* test will be employed for parametric or nonparametric analyses, respectively.

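### Pretests on the trial data choose between comparing means and comparing ranks, so the hypothesis and effect measure for VPI, and for a short ICDAS score, are not fixed in advance

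*Protocol article*

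**What the plan says.** Data Analysis sets the selection rule: "The Kolmogorov-Smirnov and Levene tests will be used to analyze the normality and homogeneity of data, determining further statistical tests". The Abstract (Methods) gives the two candidates: "A Student t test or Mann-Whitney U test will be employed for parametric or nonparametric analyses, respectively". No outcome or visit has a fixed test. The same section says "Statistical analysis will be performed using SPSS Statistics software 21.0", without naming the form of the Kolmogorov-Smirnov test.

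The scales appear under Eligibility Criteria:
- **VPI** rests on "observation of visible plaque on the buccal dental surfaces of 6 deciduous teeth".
- **CPITN**: "this study will classify deciduous teeth with 1 of 3 different scores", namely 0, 1 or 2.
- **ICDAS** is an ordered code, and entry requires "children with a score ≤3, according to the criteria of ICDAS".

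Study Outcome Measures places these three indices at "baseline and 3-, 6-, 9-, and 12-month follow-ups". eHEALS and GSES are taken only at baseline and 12 months.

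**The concern.** A normality pretest is informative only if normality is in doubt. Here it is not: a per-child VPI count has at most seven values, a CPITN score has three, and ICDAS is a short ordered code. A pass means that the sample was too small or the test too weak to see a known departure. A fail means the reverse.

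The outcome of that check then decides what is tested. The t test compares means; Mann-Whitney compares ranks. They answer different questions and come with different effect measures. Because the check would be repeated on each visit's data, one index could be reported as a mean difference at 3 months and as a rank comparison at 12 months, and the two results could not be set side by side. An unstated software option could also decide which primary test is run.

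The rule is written into the text as the analysis, so this is not a gap that a separate analysis plan would simply fill.

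**Working it through.** **Inputs from the protocol.** There are 104 dyads, 52 per group, 30% attrition and four follow-up visits. VPI is read on 6 teeth, CPITN is 0/1/2, and ICDAS is at most 3 at entry. Completers: 104 × 0.7 = 72.8, about 36 per arm. Multiple imputation, which the plan prescribes when data are not missing completely at random, would keep 52 per arm, so both sizes were run.

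**Assumptions.** The protocol gives no outcome distributions. Those below were chosen to fit its scales. Both arms have the same distribution (no treatment effect). Normality is tested in each arm at 5%, and an outcome passes if both arms pass. There are 1,000 simulated trials per scenario, so the Monte Carlo error is at most √(0.5 × 0.5 / 1000) ≈ 0.016.

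**Step 1. How often does normality pass?**

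| Outcome (assumed distribution) | 36/arm, plain KS | 36/arm, Lilliefors | 52/arm, plain KS |
|---|---|---|---|
| VPI, Binomial(6, 0.5) | 70% | 0% | 30% |
| VPI, Binomial(6, 0.3) | 46% | 0% | 6% |
| VPI, beta-binomial(6; 1, 1) | 95% | 5% | 80% |
| ICDAS maximum 0–3 (0.2, 0.3, 0.3, 0.2) | 36% | 0% | 0.5% |
| CPITN 0/1/2 (0.5, 0.4, 0.1) | 0% | 0% | 0% |
| eHEALS-like sum 8–40 | 99.9% | 82% | 99.9% |

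For Binomial(6, 0.4) at 36 per arm, separate runs sent 44% to 46% of trials to Mann-Whitney with the plain form and 100% with Lilliefors. Levene fails in a further 4% to 8% of runs.

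For VPI and the short ICDAS score, the choice therefore turns on the form of the test and on the number analysed. With Binomial(6, 0.5), the same population passes in 70% of trials at 36 per arm and 30% at 52.

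**Step 2. How often does the verdict differ between visits?** With pass probability p at each of four independent visits, P(mixed) = 1 − p⁴ − (1 − p)⁴. Plain KS, 36 per arm:
- VPI, Binomial(6, 0.5): 1 − 0.704⁴ − 0.296⁴ = 0.75
- VPI, Binomial(6, 0.3): 1 − 0.462⁴ − 0.538⁴ = 0.87
- VPI, beta-binomial: 1 − 0.946⁴ − 0.054⁴ = 0.20
- ICDAS maximum: 1 − 0.356⁴ − 0.644⁴ = 0.81
- CPITN: 0

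At 52 per arm the three VPI values are 0.75, 0.21 and 0.60, and ICDAS falls to 0.02. Under Lilliefors, the two binomial VPI cases and ICDAS never switch, because they always fail.

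**Step 3. Does correlation between visits remove the problem?** With correlated visits for a VPI-like outcome under plain KS (600 trials each), the mixed share was 86% at correlation 0, 86% at 0.5 and 83% at 0.7.

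**Step 4. Is the type I error affected?** Setting: 36 per arm, plain KS plus Levene, t test only if both pass, 4,000 trials, Monte Carlo error √(0.05 × 0.95 / 4000) ≈ 0.003.

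| Outcome | Pretest rule | Mann-Whitney fixed in advance | t and Mann-Whitney disagree |
|---|---|---|---|
| VPI, Binomial(6, 0.5) | 0.043 | 0.043 | 1.3% |
| VPI, beta-binomial | 0.055 | 0.055 | 0.7% |
| CPITN | 0.053 | 0.053 | 1.4% |
| Skewed surface count | 0.042 | 0.048 | 3.7% |

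A further run gave 0.036 to 0.058 for the pretest rule, with disagreement in about 1% to 5% of null trials.

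**The case against.** The strongest reply is that little harm follows. The pretest rule holds its nominal level, and the two tests rarely disagree on significance when there is no effect. That stands. A reader might infer that reported P values are invalid because the selection step is ignored, but the simulation does not support this.

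A second reply is that switching is not general, and this also stands in part. CPITN as a single 0/1/2 score always fails normality and stays with Mann-Whitney. VPI rarely or never switches under Lilliefors at 36 per arm. ICDAS at 52 per arm switches in about 2% of trials. A reader might infer that every oral index would change test from visit to visit, or that 87% is a general rate. It is the top of a range that depends on the assumed distribution, the form of the test and the number analysed. Correlation between visits lowers it somewhat, but not much in the case examined.

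Third, Eligibility Criteria gives no child-level summary for ICDAS or CPITN, so those rows rest on assumed summaries, and an exact model for each outcome is partly the sponsor's choice. That limits how specific the remedy can be.

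None of this defends the rule itself. It asks the data a question whose answer is already known and lets the reply set the hypothesis. Nor does non-normality by itself rule out comparing means, which is a further reason not to let a normality test decide.

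**Conclusion.** The point holds as a matter of an unfixed hypothesis and effect measure. It should be corrected, but it does not invalidate the error rate. It bears on VPI and on ICDAS if summarised as a short score. CPITN as a single score is unaffected by switching, and eHEALS and GSES sums can be near normal.

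At 36 per arm with Binomial(6, 0.4), the form of the Kolmogorov-Smirnov test alone moves the share of trials analysed by Mann-Whitney from about 45% to 100%. Under the plain form and independent visits, VPI would be tested by a mixture of methods across the four follow-ups in roughly 20% to 87% of trials. These figures rest on assumed distributions, on pretests run separately in each arm at 5%, and on 36 or 52 analysed per arm. The qualitative conclusion needs only the stated scales and the stated rule.

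**What to change.** Delete the Kolmogorov-Smirnov and Levene tests as the rule for choosing the analysis. Before outcome data are examined, name one analysis and one effect estimate with a 95% CI for each outcome, and use it at every visit at which that outcome is measured.

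- **VPI, eHEALS, GSES:** this can be a baseline-adjusted comparison of means with robust standard errors, which needs neither normality nor equal variances.
- **CPITN and ICDAS:** define the child-level summary first, then choose an ordinal or count model to match it, or one fixed rank test reported with its effect measure.
- **Mann-Whitney** can serve as a sensitivity analysis elsewhere.

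The cost is wording and slightly more analysis work. Recruitment, visits and measurements do not change.

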### Randomization

Parent and child dyads will be randomly assigned to test or control groups, according to the parameters of stratification, as follows: health and eHealth literacy levels of parents or caregivers and the ICDAS index, age, and gender of children. The randomization will be performed using the platform Randomization.com [24], through different block sizes for the allocation of participants. The blinding of allocations will be guaranteed by using closed and opaque envelopes, which will be maintained confidential by an independent researcher.

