### Sample Size

The calculation of this sample size was performed using the Open Source Epidemiologic Statistics for Public Health, following the criteria and outcomes described by Zotti et al [25]. It resulted in a total of 104 dyads of parents and children, considering a power of 80%, a significance level of 5%, and an attrition of 30%.

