Parents and caregivers seem to play an important role in the management of chronic diseases of their children [47,48], especially when these diseases affect children under 3 years, which is observed with ECC. Mobile technologies have become important resources to empower patients to be active on their own conditions through shared decision-making process [49-52]. Nevertheless, parents and caregivers could be less used to electronic devices and even less to download apps for their mobiles or tablets [47,53]. Hence, ECC-related information delivered via WhatsApp Messenger could be an alternative to engage parents or caregivers in a healthy lifestyle, contributing to a better patient-professional relationship. This app is a low-cost instant-messaging platform very popular in Latin America, and more specifically in Brazil, where 56% of the population uses it frequently [54]. According to Ojeda et al [55], WhatsApp Messenger demonstrated its effectiveness for contacting patients, independently of their education level, making it a reliable source of information and an easy way for patient-professional interaction. A previous study reported a significant reduction of dental plaque in adolescents after using WhatsApp Messenger as an adjuvant for the prevention of oral diseases [56]. However, to our knowledge, there is no evidence showing the effect of educational electronic messages sent to parents or caregivers on the prevention of ECC.

These outcomes will demonstrate the influence of educational mobile messages sent via WhatsApp Messenger on the different parameters of oral health status of children, such as biofilm accumulation, dental demineralization, gingival health, and sugar consumption. In addition, the effect of this study protocol on the levels of eHealth literacy and perceived self-efficacy of parents or caregivers will be elucidated. All aforementioned analyses will consider the effect of possible sociodemographic confounding factors, after stratifying and controlling participants according to eHealth literacy levels of parents or caregivers and the ICDAS index, age, and gender of children.

The evidence produced in this study can support the development of digital strategies to be applied in ECC preventive programs, considering their 3 main advantages: scalability, cost-effectiveness, and empowerment of laypersons for self-dental care.

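### The only between-group tests named have no covariate or stratum term, so they cannot deliver the control promised in the Discussion, and they give up power that the planned baseline data would supply

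*Protocol article*

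**What the plan says.** - **Data Analysis** (and the Methods paragraph of the abstract): the between-group comparison is a Student t or Mann-Whitney U "test will be employed for parametric or nonparametric analyses, respectively". The choice follows Kolmogorov-Smirnov and Levene results. No regression, ANCOVA, stratified test, mixed model or GEE is named. The section does not say whether the tested variable is the 12-month value, the change from baseline, or the value at each visit.
- **Discussion**: "All aforementioned analyses will consider the effect of possible sociodemographic confounding factors, after stratifying and controlling participants according to eHealth literacy levels" of parents, and the ICDAS index, age and gender of children.
- **Randomization**: the stratification factors are "health and eHealth literacy levels of parents or caregivers and the ICDAS index, age, and gender of children".
- **Study Outcome Measures**: ICDAS, VPI and CPITN are planned at baseline and at 3, 6, 9 and 12 months. Sugar consumption, eHEALS and GSES are planned at baseline and 12 months.
- **Abstract, Methods**: "The quality of randomization will be evaluated throughout the study, comparing the test and control groups systematically by Student t tests" and chi-square tests. The Data Analysis section describes the same tests on participant characteristics, without the phrase about timing.

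**The concern.** Two statements about the analysis cannot both be followed. One promises results that take account of confounders; the other names tests with no place to enter them. If this stays open, the adjusted model and its covariates may be chosen after the data have been seen.

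There is also an efficiency issue. A baseline value is planned for every outcome, and allocation is stratified on factors presumably chosen because they predict outcome. None of the named methods adjusts for either, and none models the four follow-ups of the three clinical indices together. In a trial of this size the lost precision matters.

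Finally, testing the quality of randomisation during follow-up cannot answer that question. After baseline, a difference between groups also reflects treatment and dropout.

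**Working it through.** **1. The texts side by side.** The Discussion promise has two parts. The clause about stratifying and controlling participants may describe design-stage control, which the Randomization section provides. The clause that the analyses will consider sociodemographic confounders is a promise about analysis. The sociodemographic questionnaire covers items such as race and education level, which are not stratification factors, so the design does not control them either. A two-sample t or Mann-Whitney test cannot do so.

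**2. The plan's own figure.** The Sample Size section says: "It resulted in a total of 104 dyads of parents and children", with 80% power, 5% significance and 30% attrition; the abstract adds "being divided in 52 dyads per group". No effect size or SD is given, only that the calculation was done "following the criteria and outcomes described by" a cited trial, so 104 cannot be reproduced. Back-solving (two-sided 5% and 1:1 allocation):
- 52 × 0.7 = 36.4, so about 36 completers per arm.
- Normal approximation: d = (1.960 + 0.842) × √(2/36) = 0.66; with the t distribution, 0.67.
- If attrition was instead added as 40 × 1.3 = 52, d is about 0.63. That reading also starts from 80% power, so the gains below hardly change.

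**3. Power with and without baseline.** The correlation r between baseline and 12 months is not in the document; 0.3 to 0.6 is assumed. Noncentral t, 36 per arm, noncentrality d_eff × √(36/2):
- unadjusted 12-month value: d_eff = 0.67, noncentrality 0.67 × 4.243 = 2.84, power 80%;
- baseline-adjusted: d_eff = 0.67/√(1 − r²);
- change score: d_eff = 0.67/√(2 − 2r).

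| r | d_eff, adjusted | Power, adjusted | Equivalent unadjusted n per arm, 36/(1 − r²) | d_eff, change | Power, change |
|---|---|---|---|---|---|
| 0.3 | 0.702 | 84% | 40 | 0.566 | 66% |
| 0.5 | 0.774 | 90% | 48 | 0.670 | 80% |
| 0.6 | 0.838 | 94% | 56 | 0.749 | 88% |

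A change score therefore does use baseline, but it is worse than ignoring baseline when r is below 0.5, and it trails the adjusted analysis at every r shown.

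**4. Ignoring the strata.** Simulation, 5,000 runs per setting, 36 per arm, six strata exactly balanced by arm (an assumption), with d = 0.66 for power:

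| Share of outcome variance explained by strata | Type I error, t test | Type I error, stratum-adjusted | Power, t test | Power, stratum-adjusted |
|---|---|---|---|---|
| 0 | 0.045 | 0.045 | 0.79 | 0.79 |
| 0.25 | 0.024 | 0.051 | 0.82 | 0.89 |
| 0.50 | 0.004 | 0.051 | 0.88 | 0.97 |

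The unadjusted test does not give too many false positives. It rejects too rarely, because its standard error includes between-stratum variation that the design has already removed from the comparison.

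**5. Repeated visits.** This applies only to ICDAS, VPI and CPITN. No gain is quoted for modelling the visits jointly, because it would also depend on an assumed dropout pattern.

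**The case against.** **Randomisation already protects the comparison.** This stands: the unadjusted estimate is unbiased, and the error is in the conservative direction. Stratification also limits chance imbalance on ICDAS, literacy, age and gender. A reader might infer that the unadjusted result would be biased or prone to false positives; nothing here supports that.

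**Baseline and repeated data are not shown to be thrown away.** This also stands. A reader might infer that baseline values go unused and that visits are analysed as separate snapshots. The Data Analysis section fixes neither the tested variable nor the time point. The Objectives word several hypotheses as decrease, maintenance or improvement, which a two-sample test on change could address. Baseline ICDAS and eHEALS also serve recruitment and stratification. What is established is narrower: no named method adjusts for baseline or models the visits jointly. Nor were the measurements already in hand: the Results section says that children were still undergoing baseline examination and that follow-up lay ahead.

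**Covariate choice belongs in an analysis plan that is not shown.** The list of covariates may well be there. That does not resolve a conflict between two sentences in this article.

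**The power figures rest on assumptions.** True. Entry is restricted to ICDAS scores of 3 or less, which may lower the baseline correlation, and normal-theory gains may not carry over to CPITN scored 0 to 2. At r = 0.3 the gain is only from 80% to 84%. The 36 completers describe the listwise-deletion case; multiple imputation is planned if data are not missing completely at random.

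**Balance tests are a side issue.** The phrase about testing throughout the study appears only in the abstract, and nothing says that the P values will select covariates. That use should not be inferred.

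**Conclusion.** The point holds as a contradiction with an efficiency cost. The named tests cannot carry out the adjustment that the Discussion promises, and they ignore the stratification. The comparison stays unbiased. The t test is conservative where strata are prognostic: type I error is about 0.02 if balanced strata explain a quarter of the variance and about 0.005 if they explain half. Baseline adjustment would raise illustrative power from 80% to between 84% and 94%. The contradiction needs no assumption. The sizes rest on a back-solved difference of 0.67, assumed correlations of 0.3 to 0.6, normal-theory outcomes and, for the type I error figures, six exactly balanced strata.

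**What to change.** 1. In the abstract and Data Analysis section, name one prespecified model per outcome, adjusted for the baseline value and the stratification factors actually used, with the 12-month between-group contrast as the result.
   - ICDAS, VPI and CPITN: a longitudinal mixed model or GEE with arm, visit and arm-by-visit terms, in ordinal or count form where the scale needs it. CPITN scored 0 to 2 does not suit a linear model.
   - eHEALS, GSES and sugar consumption: ANCOVA. This follows the two-time-point schedule in the body of the article; the abstract lists sugar among the three-monthly outcomes, so that schedule should be aligned too.
2. In the Discussion, either list the prespecified sociodemographic covariates or withdraw the promise.
3. Report baseline balance descriptively, and drop the testing of randomisation quality throughout the study.

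The cost is revised wording, slightly more analysis work and a few degrees of freedom. The loss from the last is negligible: at r = 0.5, power is 89.9% with 70 residual degrees of freedom and 89.8% with 64. No new data are needed. The change should be dated and made before outcomes are compared by arm.
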